#### Statistical analysis

This study will employ a three-stage analytical approach. In the first stage, baseline characteristics of study participants will be identified using descriptive statistics and standard deviations [30]. The second stage involves bivariable analysis using the chi-square test for categorical variables and the t-test for continuous variables, including the estimation of differences in proportion and mean (difference-in-difference) between intervention groups [30]. To assess the intervention's effects on primary outcomes, mixed effect regression modelling will be applied. Intervention effects will be quantified using mean differences (MD) for continuous variables and relative risks (RR) for categorical variables, along with their corresponding 95% confidence intervals (CI) [31]. The primary results will be based on adjusted effect measures, and all analyses will adhere to the intention-to-treat (ITT) principle [32]. STATA version 18 will be used for the analyses, and statistical significance will be declared by *p*-values < 0.05.

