## Methods

### Study design

This is a randomized wait-list control trial that will evaluate the effectiveness, feasibility and acceptability of online CRAFT with a parallel group. Participants will be randomised to receive either online CRAFT for 6 sessions over 6 to 10 weeks or to a wait-list control group who are provided with CRAFT related reading materials during the waiting period. Outcomes will be assessed at baseline and then at 6- and 15-weeks post baseline. Outcome measures will be completed online independently of researchers or clinicians. The trial reporting will comply with CONSORT guidelines. Figure 1 provides an overview of the trial recruitment and process.

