### Randomisation and blinding

The randomisation procedure for this project will be conducted by an independent researcher ([name]) using STATA software (Version 18 MP) and with the 'randomizr' package. This researcher will not be involved in other aspects of project implementation, such as CRAFT delivery or data collection. The researcher (NS) who recruits the participants will have no access to the order of allocation. All participants will be allocated an identification number and, before completing their baseline measures, will be randomly allocated to either the CRAFT group or the wait list control group. Individuals randomized to the control group will be assigned a 6-week wait time.

All assessments are conducted online, thus minimizing the possibility of researcher bias. Analysis of results will be blinded to the clinicians delivering CRAFT. The clinicians will be provided with contact information of consenting participants and they will deliver the program as scheduled without knowing which group the person is allocated to. Trial participants will be informed their start date for the intervention as 1. as soon as possible (Group A—within 7 days) or 2. within 6 weeks (Group B—WLC) without being informed which group they are in. The need for unblinding is not anticipated.

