#### Sample size calculation

The study's sample size is determined using data from a previously published cluster randomized trial [29]. Taking into account an outcome of treatment engagement rate of 29% for the online FEP intervention group and 15% for the control group, along with a 5% level of significance (α) and 80% power, the calculated sample size is 216 (with 108 participants in each group). To account for a conservatively estimated attrition rate of 20% during follow-up, a total of 260 participants will be recruited.

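### Stage two estimates the effect on means by difference-in-difference, which is less precise than baseline adjustment and carries any shift in the post-allocation baseline survey at full weight

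*Protocol article*

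**What the plan says.** The Statistical analysis section announces three stages. The first is descriptive. Of the second it says: "The second stage involves bivariable analysis using the chi-square test for categorical variables and the t-test for continuous variables". Effect estimates are made part of this same stage, which is described as "including the estimation of differences in proportion and mean (difference-in-difference) between intervention groups". The effect on the primary outcomes is then given to a model: "To assess the intervention's effects on primary outcomes, mixed effect regression modelling will be applied". Effects on continuous outcomes are to be reported as mean differences, and "The primary results will be based on adjusted effect measures". The section names no adjustment covariates and does not say whether the baseline score enters the model as a covariate or as one of the repeated outcomes.

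On measurement, the Study design section states: "Outcomes will be assessed at baseline and then at 6- and 15-weeks post baseline". On order, the Randomisation and blinding section says that participants, "before completing their baseline measures, will be randomly allocated to either the CRAFT group or the wait list control group". It adds: "Trial participants will be informed their start date for the intervention", which is either within 7 days or within 6 weeks. The Recruitment and follow-up procedures section gives the same sequence: verbal consent, randomisation, arranging the first appointment, and only then the link to the written consent form and the measures.

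**The concern.** Two separate matters meet in the difference-in-difference.

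The first is precision. Randomisation already makes the arms comparable in expectation, so the baseline score is useful only for removing variation between people. A change score removes it with a fixed weight of 1. Regression on baseline uses the weight that the data support, and so cannot do worse in large samples. When the correlation is low, the fixed weight adds more noise than it removes.

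The second is the status of the baseline itself. Someone who knows that counselling starts within days may answer questions on depression, anxiety, stress and life satisfaction differently from someone who knows of a six-week wait. Participants are not told their group's name, but the start date carries much the same information. The article does not show that such a shift occurs, and its direction cannot be predicted, but the order of steps permits it. An estimator that subtracts the baseline turns the shift directly into apparent effect or apparent lack of effect.

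At stake is the width and validity of the interval for the wellbeing scores. The sample size gives no separate assurance on these, because it was set on an "outcome of treatment engagement rate of 29% for the online FEP intervention group and 15% for the control group", not on a mean.

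**Working it through.** **The plan's own figure.** There is none on this point: the article gives no standard deviation, correlation or detectable difference for any scale. Its sample size supplies only the number of completers used below: 260 recruited less 20% is 208, or 104 per arm.

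**Inputs.** Let n be the number per arm and σ the SD, taken as equal in both arms and at both times. Let r be the correlation between baseline and follow-up; it is an assumption, shown from 0.3 to 0.8.

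**Variance of the between-arm estimate at one follow-up visit.**
- Follow-up score only: (2σ²/n) × 1
- Difference-in-difference: (2σ²/n) × 2(1 − r)
- Baseline-adjusted: (2σ²/n) × (1 − r²)

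The second over the third is 2(1 − r)/[(1 − r)(1 + r)] = 2/(1 + r), which exceeds 1 for every r below 1. The square root of this ratio is the ratio of interval widths. The second exceeds the first when r is below 0.5.

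**Detectable difference.** At two-sided 5% and 80% power with 104 per arm, it is (1.960 + 0.842) × √(2/104) = 0.389 SD for the follow-up score alone. The other two estimators multiply this by the square root of their variance factor.

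| r | Factor, difference-in-difference | Factor, adjusted | Variance ratio | Interval wider by | Detectable difference (SD), difference-in-difference v adjusted |
|---|---|---|---|---|---|
| 0.3 | 1.40 | 0.91 | 1.54 | 24% | 0.460 v 0.371 |
| 0.5 | 1.00 | 0.75 | 1.33 | 15% | 0.389 v 0.336 |
| 0.7 | 0.60 | 0.51 | 1.18 | 8% | 0.301 v 0.277 |
| 0.8 | 0.40 | 0.36 | 1.11 | 5% | 0.246 v 0.233 |

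At r = 0.3 the difference-in-difference (0.460 SD) is worse than ignoring baseline altogether (0.389 SD).

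**Bias from a shifted baseline.** Suppose that knowing the start date moves the mean baseline answer in one arm by d, that follow-up answers are unaffected, and that the true effect is τ.
- Difference-in-difference estimates τ − d.
- The baseline-adjusted estimate has expectation of about τ − r × d, because the regression slope is about r when the SDs are equal.
- The follow-up-only comparison estimates τ.

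For an illustrative d = 0.2 SD, the bias is 0.20 SD for the difference-in-difference. For the adjusted estimate it is 0.06, 0.10, 0.14 and 0.16 SD at r = 0.3, 0.5, 0.7 and 0.8. A simulation with 104 per arm, r = 0.6, no true effect and d = 0.2 SD (3,000 replicates) gave mean estimates of −0.20 SD for difference-in-difference, −0.12 SD for the adjusted estimate and 0.00 SD for follow-up only, in agreement with the formulas.

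**The mixed model.** Three readings fit the article's wording.
- Baseline is an outcome wave with arm means left free. With complete data, the arm-by-visit contrast against baseline is then the difference-in-difference.
- Baseline is an outcome wave with arm means constrained equal. Precision is then essentially that of the adjusted estimate, and so is the r × d exposure to a shift.
- Baseline is a covariate. This is the adjusted estimate.

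The article does not choose among them.

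**The case against.** A reader might infer that difference-in-difference is how the trial's main effect on means will be estimated, in place of baseline adjustment. The article does not support that. The term appears only in the bivariable stage, and the next sentences assign the primary outcomes to a mixed model and the primary results to adjusted measures. Only the first of the three model readings reproduces the difference-in-difference, and even then only with complete data, whereas 20% attrition is planned for. The covariate list and model form are commonly left to an analysis plan, which is not shown, so their absence is not a fault here. This objection stands in full and limits the point to stage two.

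A reader might also infer that baseline adjustment cures the bias from a late baseline. It does not: by the formula above it keeps a share r of the shift, 70% at r = 0.7. The cause is the order of survey and allocation, and only a change of order removes it.

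Two further objections carry weight. The size of the loss depends on a correlation that the article does not give, and is modest if r is high. And because the survey follows randomisation, some randomised participants may have no baseline; the article plans reminders and calls for such cases. A model with baseline as covariate would drop them unless their values are imputed, which bears on the intention-to-treat commitment.

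None of this removes what the article does state: a difference-in-difference estimate of a randomised effect, from a baseline taken after allocation. Printed beside the model-based effect on the same outcome, it could differ from it for no reason but method.

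**Conclusion.** The point holds for stage two. The difference-in-difference named there is less precise than baseline adjustment for any r below 1, with intervals about 24%, 15% or 8% wider at r = 0.3, 0.5 or 0.7. These figures assume equal SDs. Whether the primary mixed model shares the loss cannot be told from the article.

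The timing of the baseline survey is stated in the article, and it opens a route to bias: a shift d enters a difference-in-difference in full and a baseline-adjusted estimate at about r × d. That a shift occurs is a possibility, not a finding, and the 0.2 SD used above is illustrative. The follow-up-only comparison is free of this bias only if the shift is confined to the baseline answers.

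Both matters merit a change, because the remedies are cheap. Neither shows that the primary analysis is wrong.

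**What to change.** 1. **Estimator.** Drop difference-in-difference as an effect estimate and keep stage two descriptive. State that the mean difference comes from the mixed model with arm, visit, arm-by-visit and the baseline value of the same outcome as covariate, with the follow-up waves as outcomes. A model with baseline as an outcome wave and arm means constrained equal is an equivalent choice, and it keeps randomised participants whose baseline is missing. State which is used and, if the covariate form is chosen, how missing baseline values are handled.

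2. **Order of steps.** For participants still to be recruited, have the baseline survey completed before allocation and start date are disclosed. For those already enrolled, report a follow-up-only comparison as a sensitivity analysis, since it does not use the baseline answers.

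The first change costs wording and a rule for missing baselines; it needs no added participants, visits or measures. The second is a small procedural change: consent and survey would have to be complete before the participant learns the start date.

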**Methods:**

The trial is a randomized wait-list control trial assessing the effectiveness, feasibility and acceptability of online CRAFT with a parallel group. Participants will be randomised to receive either online CRAFT or to a wait-list control group who are provided with CRAFT related reading material during the waiting period. Outcomes will be assessed at baseline and then at 6- and 15-weeks post baseline. The primary outcome will be improved wellbeing of participating family members. The trial reporting will comply with SPIRIT guidelines.

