### Objectives of the study

This trial will determine the effectiveness of an online delivered CRAFT counselling intervention for improving the well-being of family members with a loved one experiencing substance problems with and without co-occurring mental health problems. It is hypothesised that CRAFT implemented online by accredited therapists will be more beneficial than CRAFT self-help information provided to the wait-list group. Compared to the wait-list control group, the CRAFT group will show significant decrease in self-reported levels of depression, anxiety and stress and significant increase in life satisfaction and that these improvements will be maintained over a three-month period post intervention.

It is hypothesized that 1) improvements in depression, anxiety and stress scores as a function of CRAFT relative to the control group will be mediated by: a) acceptability of receiving support online and b) ease of access. Given the lack of information regarding implementation parameters of substance use interventions for families of people with a mental health condition, qualitative methods will explore the experiences of study participants as well as clinicians delivering the program. The study has the following specific aims:

Aim 1: determine the effectiveness of an online delivered CRAFT counselling intervention on on self-reported levels of depression, anxiety, stress and life satisfactionAim 2: qualitatively examine the paricipants’ experiences about the acceptability of receiving support onlineAim 3: qualitatively examine the clinicians’ experiences of delivering the program and feasibility

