### Depression, Anxiety, and Stress Scale (DASS-21)

The DASS-21 [20] is a 21-item self-report questionnaire designed to measure the domains of depression, anxiety and stress. Each subscale contains 7 items rated on a four-point Likert scale. Higher scores indicate more severe symptoms. The DASS-21 is reported to have high internal consistency for each of the subscales (depression, *r* = 0.88; anxiety, *r* = 0.82; stress *r* = 0.90), and the total scale (*r* = 0.93) [21].

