### The Flourishing Scale (FS)

The FS is an eight item self-report measure of psychological well-being [24]. The scale concepts include feelings of competence, positive relationships, and purpose in life. Respondents rate on a 7-point Likert scale from strong disagreement to strong agreement with statements. Scores range from 8 to 56 and high scores indicate positive self report of wellbeing [25]. The scale developers report strong correlations with other psychological well-being scales and good internal consistency with Cronbach’s alpha coefficient of 0.87 [24].

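### The primary outcome is wellbeing with no named score or visit, singular in one section and plural in another, so the 5% error rate for the main claim is not fixed

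*Protocol article*

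**What the plan says.** All references are to the protocol article.

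- **Abstract, Methods:** "The primary outcome will be improved wellbeing of participating family members". This is one outcome, stated as a construct, with no instrument, score or visit.
- **Statistical analysis:** "To assess the intervention's effects on primary outcomes, mixed effect regression modelling will be applied". Here the outcomes are plural and are not listed. The section sets a single significance threshold of p < 0.05 and reports 95% confidence intervals.
- **Objectives of the study:** compared with the wait-list, "the CRAFT group will show significant decrease in self-reported levels of depression, anxiety and stress and significant increase in life satisfaction". Aim 1 lists the same four scores.
- **DASS-21:** one questionnaire, "designed to measure the domains of depression, anxiety and stress". Three of the four scores therefore come from one instrument and the fourth from the SWLS.
- **The Flourishing Scale:** "The FS is an eight item self-report measure of psychological well-being". Table 1 gives it the same domain label as the DASS-21 and places the SWLS under quality of life.
- **Study design:** "Outcomes will be assessed at baseline and then at 6- and 15-weeks post baseline". Neither follow-up visit is named as primary.
- **Sample size calculation:** this uses a treatment engagement rate (29% v 15%), so it does not identify the primary score either.

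No section ranks the scores, splits the significance level, or says how several scores combine into one conclusion about wellbeing.

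**The concern.** The trial's main conclusion will be that CRAFT does or does not improve family members' wellbeing. A 5% error rate for that conclusion needs one test, or a stated rule for several. The document offers four scores, or five with the Flourishing Scale, each at two visits and each judged at the same threshold. Two readers could follow it faithfully and reach different headline results from the same data.

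At stake are the false-positive rate, if any one score is enough, or the power, if all are needed. On this text, nothing prevents the score and visit that carry the claim from being settled once results are known. The preliminary analysis described under Trial duration also refers to participant wellbeing without naming a score.

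**Working it through.** **Inputs from the document.** Four scores in the hypothesis, or five with the Flourishing Scale. Two follow-up visits. Threshold 0.05 per test. 108 per group before attrition, 80% power. Sidedness is not stated; the 95% confidence intervals imply two-sided tests, which are used below.

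**Input that is assumed.** The correlations between scores. The document gives none, so a range is shown.

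**Step 1: the plan's own figure.** With p1 = 0.29, p2 = 0.15 and mean 0.22, the standard formula is n = [z_α √(2 × 0.22 × 0.78) + 0.842 √(0.29 × 0.71 + 0.15 × 0.85)]² / 0.14².

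- One-sided 5%: [1.645 × 0.586 + 0.842 × 0.577]² / 0.0196 = 107.2, so 108 per group and 216 in all. This matches.
- Two-sided 5%: [1.960 × 0.586 + 0.842 × 0.577]² / 0.0196 = 136.3, so 137 per group.

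The stated number therefore reproduces only as a one-sided test, and on an outcome that is not a wellbeing score. It settles neither the primary score nor the sidedness of its test.

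**Step 2: any one of four scores is enough, one visit.** If independent: 1 − 0.95⁴ = 0.185. With correlated scores, by simulation of two-sided tests on normal statistics (1 million draws):

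| Common correlation | Chance of at least one false positive |
|---|---|
| 0 (exact) | 18.5% |
| 0.3 | 17.4% |
| 0.5 | 15.6% |
| 0.6 | 14.4% |
| 0.7 | 13.1% |
| 0.8 | 11.4% |

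A more realistic pattern has the DASS-21 subscales correlated 0.5, 0.6 or 0.7 with each other and the SWLS correlated −0.3, −0.4 or −0.5 with them. It gives 16.5%, 15.4% and 14.2%.

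These figures count errors in either direction, as the nominal 5% does. Counting only errors in favour of CRAFT, the nominal rate is 2.5% and the independent figure is 1 − 0.975⁴ = 9.6%, so the relative inflation is similar.

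**Step 3: wider sets, same rule.**

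- Adding the Flourishing Scale: 1 − 0.95⁵ = 22.6% if independent, about 17% to 20% under the mixed pattern.
- Four scores at both visits, with an assumed between-visit correlation of 0.6: about 24% to 27%.

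**Step 4: all four scores must be significant.** The error rate is then at most 5%. Power falls instead. If each score had 80% power and the scores were independent, it would be 0.8⁴ = 41%. Correlation raises this, but never above 80%.

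**Step 5: with the rule fixed.** One named score at one visit gives 5%. Bonferroni over four, at 0.05/4 = 0.0125 each, gives 1 − 0.9875⁴ = 4.9% if independent and at most 5% under any correlation. With 108 per group and 80% power, the detectable difference is:

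- (1.960 + 0.842) × √(2/108) = 0.38 SD at two-sided 0.05;
- (2.498 + 0.842) × √(2/108) = 0.45 SD at two-sided 0.0125.

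**The case against.** **The hypothesis joins its outcomes with an and.** It predicts "significant decrease in self-reported levels of depression, anxiety and stress and significant increase in life satisfaction". Read literally, all four must succeed, and then no error is inflated. This stands as a possible reading, and the inflation figures are conditional on the other one. However, it is a prediction, not a decision rule. It also does not fit an abstract with a single primary outcome.

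**The analysis plan and the full protocol are not shown.** A multiplicity procedure or an order for secondary endpoints could sit there, and its absence here is not a finding. What stands is narrower. The abstract and the Statistical analysis section disagree on whether there is one primary outcome or several, and neither says which score or visit it is. That has to be reconciled whatever another document adds.

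**Stronger readings that the document does not support.**

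- A reader might infer that the primary effect is a simple difference in change scores, from "including the estimation of differences in proportion and mean (difference-in-difference) between intervention groups". That phrase belongs to the second, bivariable stage. Effects on primary outcomes come from the mixed model, and the primary results rest on adjusted estimates, so no loss of precision follows.
- A reader might add the Brief-COPE subscales to the count. Table 1 places that scale under stress and distress management, and it is absent from the hypothesis and Aim 1.
- A reader might treat the two visits as two looks at the same contrast. Controls wait six weeks, so by week 15 the comparison may be immediate against delayed CRAFT. The two-visit figure in Step 3 is valid only when CRAFT has no effect at all.

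**Conclusion.** The point holds as an unresolved definition of the primary outcome. If one significant score is enough, the chance of a false positive at one visit is about 11% to 19% for four scores, over correlations from 0.8 down to 0. That is more than twice the nominal 5% throughout the range. It is higher with the Flourishing Scale or the second visit. If all four scores are required, the error rate is held and the cost is power.

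A reader might infer that the trial's error rate simply is 15% to 19% rather than 5%. The document does not support that: it states no rule under which one score wins, the correlations are assumed, and at 0.7 to 0.8 the figure is 11% to 13%. The firm conclusion is that a 5% rate for the wellbeing claim cannot be derived from the plan as written. This should be corrected. It does not invalidate the design.

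**What to change.** Reconcile the Abstract, Objectives of the study and Statistical analysis sections before any unblinded analysis, including the preliminary one. Either route works:

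1. **One primary.** Name one score at one visit, tested at two-sided 5%. DASS-21 total at week 6 is an example, since week 6 is the last visit before controls are due to start CRAFT.
2. **Four co-primaries.** Keep depression, anxiety, stress and life satisfaction at one named visit, with Holm or with Bonferroni at 0.0125 each. Under Bonferroni the detectable difference rises from 0.38 to 0.45 SD at 108 per group.

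Under either route, list the other scales and week 15 as secondary.

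The change is to wording and the registry entry, but it has costs:

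- Secondary scales can no longer carry the headline claim.
- CRAFT runs over 6 to 10 weeks, so some participants will still be in the programme at week 6.
- Recruitment began in October 2023, so the primary outcome is clarified after the start. The date and reason should be recorded.
- The maintenance hypothesis at week 15 becomes secondary.
- The sample size was set on treatment engagement, so the detectable difference for the chosen score should be stated.
- Baseline measures are completed after allocation. If the adjusted model uses the baseline score, that ordering should be acknowledged.
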